### Design

2.1

All patients are recruited from community residents in the Hongkou and Yangpu districts of Shanghai voluntarily. After obtaining informed consent, they are randomly assigned to either control group or experimental group: control group receive a simplified WQXs intervention, which is refer to as WG, and experimental group receive a combination of simplified WQXs and MT intervention, which is refer to as WMG. The study observation period was 24 weeks. The range of motion (ROM) of the lumbar spine in flexion, extension, and lateral flexion was measured using an electrogoniometer. Pain and the quality of life of patients with chronic low back pain is assessed using scales such as the visual analogue scale (VAS) and the SF-36 questionnaire. The mechanical properties of the lumbago core muscles are evaluated using surface electromyography and isokinetic muscle strength tests to explore the underlying biomechanical mechanisms and enhance clinical efficacy. The following covariates were collected at baseline: age, sex, body mass index (BMI), occupational type (sedentary/manual labor), daily physical activity level, disease duration, and history of low back pain. The impact of these factors on low back pain was analyzed (Figure 1).

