#### WQXs

2.5.1

The movements of tiger play (tiger lift, tiger pounce), deer play (necked deer, necked deer) and bear play (bear shake, bear movement) are selected as the basis for the exercise routine design.

The initial phase consists of a 5-min preparatory warm-up session, followed by a 20-min simplified WQXs exercise targeting the core muscles of the low back and abdomen. Subsequently, the third stage involved a 5-min relaxation training component within the simplified WQXs regimen. In the simplified WQXs training for the core muscles of the lumbar and abdominal regions, a standing and moving position is used, Perform 3 sets of each movement, with 15 repetitions per set, maintaining each repetition for 5 s, and allow a 30 s rest interval between sets. A course of 5 sessions/week, combined with health education and a 2-day break between sessions, The study observation period spanned 24 weeks, comprising a 1-week intervention phase followed by follow-up assessments at weeks 6, 12, 18, and 24 (Figure 2).

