### Outcome measures

2.6

During the cycle, participants will undergo an initial assessment at baseline within one week of enrollment, followed by follow-up evaluations at four time points: 0 weeks, 6 weeks, 12 weeks, and 24 weeks. The primary outcome is lumbar lordosis mobility. Secondary outcomes include surface EMG, isometrics muscle strength, the Depression Self-Rating Scale, theVAS score, score of the JOA Lower Back Pain Rating Scale, score of the Oswestry Lumbar Functional Index Questionnaire, score of the SF-36 Healthy Quality of Life Scale, and score of the Pittsburgh Sleep Quality Inventory (PSOI).

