### Statistical analysis plan

2.11

According to the Case report form (CRF) table, after each measurement, the data are double-entered into Stata software within one week, and the data are processed and analyzed using SPSS26.0 statistical software. Measurement data are expressed as mean ± standard deviation, and the *t*-test is used if the data meet the normal distribution, and the rank-sum test is used if the data do not meet the normal distribution and the chi-square test was used for comparison of count data. *α* = 0.05 was used as the test level for significant differences.

If there are intolerable or serious adverse reactions during exercise, the trial will be discontinued; however, those who have participated in more than 1 cycle of exercise should be counted for efficacy. Volunteers who are unwilling to continue the clinical trial during the trial and take the initiative to ask the investigator to discontinue the trial could discontinue the trial. In case of discontinuation, more than 1/2 of the data are analyzed and less than 1/2 are excluded.

If imbalances exist between the two groups at baseline regarding variables such as gender, occupation, and physical activity, Analysis of Covariance (ANCOVA) with covariate adjustment will be employed as a sensitivity analysis。

Recognizing that age may influence musculoskeletal elasticity, the speed of rehabilitation response, and compliance, we performed a stratified analysis by age (e.g., <40 years vs. ≥40 years) in addition to conventional analyses, to examine whether there was a significant interaction effect of the intervention across different age groups.

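### The main comparison of lumbar range of motion (ROM) names no baseline ROM term and lets a normality check choose the test; a pre-specified baseline-adjusted ANCOVA would be more precise at almost no cost

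*Protocol article*

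**What the plan says.** All of the following is in the protocol article.

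- **Main test (2.11).** The t-test "is used if the data meet the normal distribution"; otherwise "the rank-sum test is used if the data do not meet the normal distribution". No covariate is attached to either test.
- **Adjustment (2.11).** The condition is "If imbalances exist between the two groups at baseline regarding variables such as gender, occupation, and physical activity". When it is met, "Analysis of Covariance (ANCOVA) with covariate adjustment will be employed as a sensitivity analysis". Baseline ROM is not among the examples.
- **Covariates collected (2.1 Design).** The list is "age, sex, body mass index (BMI), occupational type (sedentary/manual labor), daily physical activity level, disease duration, and history of low back pain". Baseline ROM is not in it.
- **Baseline assessment (2.6 Outcome measures).** "participants will undergo an initial assessment at baseline within one week of enrollment", so a baseline ROM value should exist for each patient.
- **Visits.** Section 2.6 gives "follow-up evaluations at four time points: 0 weeks, 6 weeks, 12 weeks, and 24 weeks", whereas section 2.5.1 (WQXs) gives "follow-up assessments at weeks 6, 12, 18, and 24". No primary visit is named.
- **Primary outcome.** Section 2.6 names mobility of the lumbar lordosis; section 2.10 (Sample size) is built on forward-flexion ROM.

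**The concern.** The baseline value of a continuous outcome usually predicts its follow-up value. Leaving it out of the main comparison leaves explainable variation in the error term, which matters in a trial of 74 patients that the article itself calls modest in size.

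Two features of section 2.11 add to this. First, adjustment is tied to observed imbalance, with no threshold and an open list of variables, so whether it is done and for what is settled after the data are seen. Second, the normality check decides whether the main result is a difference in means or a comparison of ranks. These answer different questions, and only the first corresponds to the difference used to size the trial.

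At stake are the precision of the main estimate and a clear statement, in advance, of what is being estimated.

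**Working it through.** **Inputs.** From section 2.10: means 46.20 and 42.59, SDs 5.25 and 5.14, 33 per group, 10% dropout, 74 in total. From section 2.11: α = 0.05. Two-sided testing and 80% power are not stated; they are inferred because they reproduce the stated size. The correlation r between baseline and follow-up ROM is **assumed**, over a range of 0.2 to 0.7.

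**Step 1: reproduce the plan's figure.**
- Difference = 46.20 − 42.59 = 3.61.
- Pooled SD = √[(5.25² + 5.14²)/2] = 5.195.
- d = 3.61/5.195 = 0.695.
- n per group = 2(1.960 + 0.842)²/0.695² ≈ 32.5, rounded up to 33.
- Total = 66/0.9 = 73.3, rounded up to 74.

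The planned size is therefore that of an unadjusted two-group comparison. The exact t-test calculation needs 33.5 per group, and exact power at 33 per group is 79.4%.

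**Step 2: adjust for baseline ROM.** ANCOVA multiplies the residual variance by 1 − r², so the effective standardised difference is d/√(1 − r²). A change-score analysis, with equal SDs at the two times, has variance factor 2(1 − r), so its effective difference is d/√[2(1 − r)]. Power below is t-based, two-sided 5%, 33 per arm. The single degree of freedom spent on the covariate changes no rounded figure.

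| r (assumed) | 1 − r² | d, ANCOVA | Power, unadjusted | Power, ANCOVA | Power, change score |
|---|---|---|---|---|---|
| 0.2 | 0.96 | 0.709 | 79.4% | 81.0% | not tabulated |
| 0.3 | 0.91 | 0.728 | 79.4% | 83.0% | 65% |
| 0.5 | 0.75 | 0.802 | 79.4% | 89.4% | 79% |
| 0.7 | 0.51 | 0.973 | 79.4% | 97.3% | 95% |

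ANCOVA is at least as powerful as either alternative in every row, because 1 − r² never exceeds 1 or 2(1 − r).

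**Step 3: effect of the normality check on error rates.** A simulation with 33 per group, no treatment effect, and a Shapiro test in each group choosing between t-test and rank-sum test (10,000 runs per distribution) gave type I error of 5.1% (normal), 4.8% (lognormal) and 4.7% (exponential). The check does not inflate the error rate. What it changes is the quantity reported.

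**Step 4: chance baseline imbalance.** In an unadjusted comparison of follow-up values with equal SDs, about r times a chance baseline difference carries into the estimate. Taking the follow-up SD as the baseline SD, one standard error of baseline imbalance is 5.195 × √(2/33) = 1.28. At r = 0.5 this moves the estimate by about 0.64, which is 18% of the planned 3.61. The unadjusted standard error already allows for such shifts; ANCOVA removes them.

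**The case against.** The strongest reply is that nothing here is invalid. Randomisation makes the unadjusted estimate unbiased, its standard error covers chance imbalance, and the sample size was computed for exactly this test. All of that stands. The gain also depends on a correlation the article does not report: at r = 0.2 it is under two percentage points. That stands too, and is why a range is shown.

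A second reply is that the full analysis plan may hold more detail. It may, but section 2.11 does choose the test, the rule for switching tests, and the conditional, secondary place of ANCOVA. These are stated choices, not details left for later.

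Several stronger readings are tempting and are not supported:

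- **That each visit is tested separately, with multiplicity as a result.** Section 2.11 does not say how visits enter the analysis.
- **That baseline ROM is certainly discarded.** Section 2.11 does not say whether raw values or changes are tested. The Discussion (section 5) speaks of comparing changes between the groups, though in relation to mechanisms. If changes are tested, baseline is used, but less efficiently than in ANCOVA. The list of adjustment variables is also open, so baseline ROM is unnamed but not excluded.
- **That a baseline difference passes in full into the estimate.** Only about r times it does.
- **That the imbalance trigger alters the main result.** It governs a sensitivity analysis only.
- **That the normality check inflates false positives.** The simulation shows it does not.
- **That age is examined only by separate strata.** Section 2.11 already plans to look for an interaction with age group.

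**Conclusion.** The point holds as a worthwhile, nearly free improvement, not as an error that invalidates the analysis. The stated main test names no baseline ROM term, and the trial data choose between two different target quantities.

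With 33 per arm and the planned effect, pre-specified adjustment raises power from 79% to between 81% and 97% for r from 0.2 to 0.7. If change scores were intended, the comparison is with 65%, 79% and 95% at r = 0.3, 0.5 and 0.7, and ANCOVA still does better (83%, 89% and 97%). These figures assume the means and SDs of section 2.10, equal SDs at baseline and follow-up, a linear relation, and 33 evaluable patients per arm. The description of the plan is firm; the size of the gain is not, because r is unknown.

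**What to change.** 1. First reconcile sections 2.6 and 2.10 so that one ROM measure is the primary outcome, and sections 2.5.1 and 2.6 so that there is one visit schedule. Name one primary visit.
2. Before any look at outcomes by arm, specify the primary analysis as ANCOVA of that ROM outcome on arm and baseline ROM. The equivalent repeated-measures mixed model, with the arm contrast at the named visit, would also serve.
3. Apply it regardless of observed imbalance or normality tests, and report the adjusted mean difference with its 95% confidence interval.
4. Keep the unadjusted t-test and the rank-sum test as sensitivity analyses.

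This needs no extra patients and no extra measurements: the model uses the baseline assessment already planned. The cost is a dated amendment and the work of settling item 1. Section 2.3 puts the start of enrolment in September 2023 and parts of section 2.11 are in the past tense, so the amendment should state whether outcome data by arm had been seen when the change was made.

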### Sample size

2.10

In this study, the formula for calculating the sample size for the two-sample test of variance was used, with lumbar anterior flexion range of motion as the main effector, and referring to the literature report and the result of the pre-test, the range of motion of lumbar anterior flexion in the two treatment groups was 46.20 ± 5.25 and 42.59 ± 5.14 (26), respectively, which was calculated to require 33 patients in each group. Accounting for an anticipated 10% dropout rate, the total sample size needed is 74 participants.

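### Section 2.11 seeks a treatment-by-age interaction through an age-stratified analysis with an open cut-point, and names no test that yields an interaction estimate

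*Protocol article*

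**What the plan says.** All of the relevant analysis text is in section 2.11 (Statistical analysis plan) of the protocol article.

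- **Method for the age question:** "we performed a stratified analysis by age (e.g., <40 years vs. ≥40 years) in addition to conventional analyses".
- **Its purpose:** "to examine whether there was a significant interaction effect of the intervention across different age groups".
- **Tests named:** a t-test for normally distributed measurements, otherwise "the rank-sum test is used if the data do not meet the normal distribution", and chi-square for counts. The significance level is stated as "0.05 was used as the test level for significant differences".
- **Only model named:** if the arms differ at baseline on variables such as gender, occupation or physical activity, "Analysis of Covariance (ANCOVA) with covariate adjustment will be employed as a sensitivity analysis". It is not tied to age or to a product term.

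Section 2.1 lists age among the covariates collected at baseline, and the eligibility criteria admit ages 18 to 60. The share of patients under 40 is not given.

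**The concern.** The section names a method and a purpose, and the method as named does not reach the purpose. An interaction is a difference between two treatment effects. Testing it needs an estimate of that difference and its standard error. A t-test, rank-sum test or chi-square test applied to two arms supplies neither, whether it is run on everyone or inside one age stratum.

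With nothing else named, an analyst could easily run the listed tests in each stratum and take a significant result in one and a non-significant result in the other as evidence that age modifies the effect. In strata this small that pattern is common when the effect is the same at every age. The trial could then report that the combined therapy works only in younger, or only in older, patients on no real evidence.

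Because the cut-point is only an example, the split could also be chosen after the data are seen.

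**Working it through.** **Inputs.** From section 2.10: "the range of motion of lumbar anterior flexion in the two treatment groups was 46.20 ± 5.25 and 42.59 ± 5.14", and "which was calculated to require 33 patients in each group". Assumed, because not stated: two-sided α = 0.05, 1:1 allocation within strata, equal SD across strata, and an age split between 50/50 and 25/75.

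**Reproducing the plan's figure.**

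- Difference: 46.20 − 42.59 = 3.61 degrees.
- Pooled SD: √((5.25² + 5.14²)/2) = 5.195. Standardised effect: 3.61/5.195 = 0.695.
- n per arm = 2(1.96 + 0.8416)²/0.695² = 32.5, so 33. Power is not stated, but 80% reproduces the 33 (90% would need 44).
- With 10% dropout, 66/0.90 = 73.3, so 74. Both figures agree with section 2.10.

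**Separate tests, same true effect in both strata.** With 66 evaluable patients split evenly there are 16.5 per arm per stratum.

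- SE of the effect in one stratum: 5.195 × √(2/16.5) = 1.81.
- Noncentrality: 3.61/1.81 = 2.00. Power of the two-sample t-test: 0.490.
- P(exactly one significant) = p₁(1 − p₂) + p₂(1 − p₁) = 2 × 0.490 × 0.510 = 0.50.

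**Interaction test.** SE = 5.195 × √(2/n₁ + 2/n₂), where n₁ and n₂ are the numbers per arm in each stratum. For the even split this is 5.195 × √(4/16.5) = 2.56, twice the main-effect SE of 5.195 × √(2/33) = 1.28. The power below is for an interaction of 3.61 degrees, that is, the whole planned effect in one stratum and none in the other (t-test, 62 df). The last column is (1.96 + 0.8416) × SE.

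| Age split | Power in each stratum | Exactly one significant, no interaction | Interaction SE | Interaction power | Interaction needed for 80% power |
|---|---|---|---|---|---|
| 50/50 | 0.490, 0.490 | 50% | 2.56 | 28.5% | 7.2 degrees |
| 40/60 | 0.403, 0.568 | 51% | 2.61 | 27.5% | 7.3 degrees |
| 30/70 | 0.310, 0.637 | 55% | 2.79 | 24.7% | 7.8 degrees |
| 25/75 | 0.261, 0.668 | 58% | 2.95 | 22.5% | 8.3 degrees |

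If all 74 patients were evaluable, discordance would be 50% to 59% and interaction power 25% to 31%.

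**Other truths, even split.**

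- No effect in either stratum: 2 × 0.05 × 0.95 = 9.5% discordant.
- Whole effect in one stratum only: 0.490 × 0.95 + 0.510 × 0.05 = 49% discordant. This is about the same as with identical effects, so the pattern hardly separates the two situations.

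**Simulation check** (40,000 trials, strata of 16 and 17 per arm): discordance was 49.7% with equal effects, 9.6% with no effect and 48.1% with the effect in one stratum only. The interaction test was falsely positive in 4.9% and had 28.5% power.

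**Continuous age.** Simulations with 66 patients and an assumed linear change of 0.15 degrees per year in the effect gave about 28% power with age in years, against 22% with the split. At 0.20 degrees per year the figures were about 46% and 35%. These slopes are illustrative and do not come from the protocol.

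**The case against.** A reader might infer that the protocol has decided to judge the interaction from separate tests in the two strata, and will therefore often report a false age difference. The document does not support that. It does not say that the t-test or rank-sum test is run within strata, or that stratum p-values are compared. It names the right target, an interaction effect. It also sets the stratified analysis alongside the conventional analyses, which are most naturally the listed two-group tests. A stratified analysis can include a formal heterogeneity test, and a separate analysis plan may specify one. The 50% figure is therefore conditional on one reading of the text, and also on the treatment having its planned effect.

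The gain from continuous age is conditional too. It rests on assumed slopes and on exactly linear modification, which favours that model.

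These limits are accepted. What stands is narrower: the section does commit to a route to the interaction, none of its named tests delivers one, and its cut-point is explicitly left open. That is a stated choice fixed badly, not merely detail left to another document.

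**Conclusion.** The point holds in limited form. Section 2.11 pairs an interaction aim with a stratified analysis, two-group tests and an example-only cut-point, and leaves unsaid how the strata will be compared.

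If the named tests were applied within strata and their p-values compared, about 50% to 58% of trials would show exactly one significant stratum with no age effect present, against 5% for a proper interaction test. This rests on a true effect of 3.61 degrees at every age, a common SD of about 5.2, 33 evaluable per arm, two-sided α of 0.05 and the assumed age splits. With no treatment effect the figure is about 10%.

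Even the proper test is weak here, with about 22% to 28% power for an interaction as large as the planned effect. A non-significant result would therefore not show that the effect is the same at all ages.

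Severity is minor. The analysis is supplementary, and neither the primary comparison nor the sample size depends on it.

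**What to change.** In section 2.11:

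- State that effect modification by age is judged by an arm-by-age term in one linear model for flexion range of motion, preferably with age in years, and report the coefficient with its 95% CI.
- Label the analysis exploratory and say that power for it is low.
- Fix the cut-point in advance by removing the wording that makes 40 years an example. Show the two stratum estimates with confidence intervals for description only, and draw no conclusion from within-stratum p-values.

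The cost is about two sentences. Age is already collected at baseline, so no new data, patients or visits are needed.

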## Ethics and dissemination

3

### Ethics

3.1

This project was approved by the Research Ethics Committee of the Fourth People's Hospital of Shanghai Tongji University (No. 2022115-001). All experimental studies were conducted in accordance with the regulations of the Research Ethics Committee of the Fourth People's Hospital affiliated to Tongji University

### Data management and trial monitoring

3.2

#### Data collection

3.2.1

Before the initiation of data management for clinical trials, it is imperative to formulate a plan based on the unique characteristics of the research endeavor. The development of a (CRF), design, and completion of this document, as well as its subsequent submission, fall under the purview of the sponsor, commissioned by the Clinical Research Organization the investigators, data management specialists, and statisticians. The design of the database should be anchored in the CRF of the project, with careful attention paid to the receipt and entry of test data. To ensure double-entry accuracy, verifiable measures must be implemented to verify data integrity, including randomization, enrollment, exclusion criteria, time windows, logic, and extreme values. Additionally, challenges from clinical inspectors must be managed appropriately through signed written responses to their queries.

Data challenge forms may also be issued by clinical inspectors to both investigators and researchers. These forms require signed written answers to questions, indicating compliance with regulatory standards. Management of data challenge forms involves responding to these queries from clinical investigators and researchers while maintaining the confidentiality of patient information.

#### Quality control

3.2.2

During the execution of the study, strict quality control measures are implemented at every stage to guarantee scientific rigor, safety, and accuracy. These stages include patient inclusion according to diagnostic criteria, study inclusion/exclusion criteria, determination of sample size, randomization, single-blind methodology, statistical analysis methods, and more. Before conducting the pilot study, personnel involved in the study receive comprehensive training. All measurements were independently performed by two standardized assessors, and the mean values were adopted. Comprehensive rehabilitation training and assessment are conducted by primary therapists, while animal play demonstrations and imagery training are performed by trained instructors using Five Animal Play methodologies. This ensures that the quality of movement and training content is robust and effective.

From patient inclusion until the implementation of the intervention, hospitalized physicians and rehabilitation therapists collaborate closely with patients, patiently explaining the role of exercise imagery intervention in a clear and understandable manner. This approach fully motivates patients to actively participate in treatment programs, ultimately contributing to the success of the research endeavor.

